## Study Identification

Unique Protocol ID: NO.2020QN80

Brief Title: COVID-19 Lockdown Related Telemedicine for Type 2 Diabetes

Official Title: Impact of Telemedicine on Young and Middle-aged Obese Patients With Type 2 Diabetes Mellitus During COVID-19 Pandemic

Secondary IDs:

## Study Status

Record Verification: January 2021

Overall Status: Completed

Study Start: January 5, 2021 [Actual]

Primary Completion: December 5, 2021 [Actual]

Study Completion: February 5, 2022 [Actual]

## Oversight

U.S. FDA-regulated Drug: No

U.S. FDA-regulated Device: No

U.S. FDA IND/IDE: No

Human Subjects Review: Board Status: Approved

Approval Number: xyy11[2020]40

Board Name: Medical Ethics Committee of Xuzhou No.1 Peoples Hospital

Board Affiliation: Xuzhou No.1 Peoples Hospital

[contact]

Email: [contact]

Address:

[name]

Data Monitoring: No  
FDA Regulated Intervention: No

## Study Description

**Brief Summary:** At present, in order to cope with the global pandemic of the COVID-19 virus, governments have introduced corresponding measures, COVID-19 lockdown is one of the most important measures. However, lockdown makes the management of chronic diseases (such as type 2 diabetes) more difficult, and telemedicine may be one of the solutions. We hope to explore the effect of telemedicine on blood glucose control and other prognostic indicators of young and middle-aged obese patients with type 2 diabetes who will experience isolation control.

**Detailed Description:** We recruit patients with type 2 diabetes who need to be isolated due to the COVID-19 epidemic, Our study will include young and middle-aged obese patients. The lockdown period is 21 days. The patients will be randomly divided into two groups with a total follow-up time of 6 months. One group is the telemedicine intervention group, and the other group is the routine follow-up control group. The intervention group used the hospital telemedicine management system to upload blood glucose values (fasting and 2h after three meals), food intake of three meals, and exercise volume (Data collection frequency: first three months, 4 times/week; 4-6 Month, 2 times/week). Doctors will collect data from hospital telemedicine management system to guide patients on diets, exercise, and medication adjustments. The control group will be followed up by telephone/outpatient clinic every 1 week. (only telephone follow-up will be conducted during the lockdown period) Then doctors will collect their blood glucose values.(fasting and 2h after three meals) Based on the data collected, The doctors will provide lifestyle guidance to the patients on the telephone or face to face. The clinical data of the two groups of patients will be collected at baseline, 22 days, 3 months, and 6 months respectively. (HbA1c, fasting blood glucose(FBG), blood glucose 2 hours after breakfast, blood pressure, Body Mass Index(BMI), waist-to-hip ratio, total cholesterol(TC), triglyceride(TG), high-density lipoprotein cholesterol(HDL-C), low-density lipoprotein cholesterol(LDL-C), Blood Urea Nitrogen(BUN), serum creatinine(Scr), e-GFR, Self-rating Depression Scale, frequency of hypoglycemia#and Cost effectiveness) The clinical data will be statistically analyzed.

## Conditions

**Conditions:** Type 2 Diabetes Mellitus  
**Keywords:** Type 2 Diabetes Mellitus  
COVID-19 lockdown  
Telemedicine  
Obesity  
Young and middle-aged

## Study Design

**Study Type:** Interventional  
**Primary Purpose:** Health Services Research  
**Study Phase:** N/A  
**Interventional Study Model:** Parallel Assignment

Number of Arms: 2

Masking: None (Open Label)

Allocation: Randomized

Enrollment: 99 [Actual]

## Arms and Interventions

| Arms                                                                         | Assigned Interventions                                                                                                                                                                                              |
|------------------------------------------------------------------------------|---------------------------------------------------------------------------------------------------------------------------------------------------------------------------------------------------------------------|
| Experimental: Telemedicine
Diabetes education and support by telemedicine | Device: Hospital telemedicine management system
Patients upload data of blood glucose, diet and exercise. Then doctors guide patients' diet, exercise and medication adjustment through the telemedicine system. |
| Active Comparator: Usual care
Diabetes education and support in person    | Usual care
Outpatient/telephone follow-up#continued care, as usual, from their primary care provider through out duration of action 6 months intervention period                                                 |

## Outcome Measures

Primary Outcome Measure:

1. Glucose control (HbA1c levels)  
Change in HbA1c among control and telemedicine groups from baseline to 6 months  
[Time Frame: Baseline, 22days,3 months and 6 months]

Secondary Outcome Measure:

2. Change in FBG  
Change in FBG among control and telemedicine groups from baseline to 6 months  
[Time Frame: Baseline, 22days,3 months and 6 months]
3. Change in Blood glucose 2 hours after breakfast  
Change in Blood glucose 2 hours after breakfast among control and telemedicine groups from baseline to 6 months  
[Time Frame: Baseline, 22days,3 months and 6 months]
4. Change in Blood pressure  
Change in Blood pressure among control and telemedicine groups from baseline to 6 months  
[Time Frame: Baseline, 22days,3 months and 6 months]
5. Body mass BMI changes  
Comparison of BMI changes among control and telemedicine groups from baseline to 6 months  
[Time Frame: Baseline, 22days,3 months and 6 months]
6. Change in waist-to-hip ratio  
Comparison of waist-to-hip ratio changes among control and telemedicine groups from baseline to 6 months  
[Time Frame: 6 months]
7. Change in biological parameter: TC  
Variation between baseline to 6 months of Biological parameter among control and telemedicine groups: TC  
[Time Frame: Baseline, 22days,3 months and 6 months]
8. Change in biological parameter: TG  
Variation between baseline to 6 months of Biological parameter among control and telemedicine groups: TG

[Time Frame: Baseline, 22days,3 months and 6 months]

9. Change in biological parameter: HDL-C

Variation between baseline to 6 months of Biological parameter among control and telemedicine groups: HDL-C

[Time Frame: Baseline, 22days,3 months and 6 months]

10. Change in biological parameter: BUN

Variation between baseline to 6 months of Biological parameter among control and telemedicine groups: BUN

[Time Frame: Baseline, 22days,3 months and 6 months]

11. Change in biological parameter: Scr

Variation between baseline to 6 months of Biological parameter among control and telemedicine groups: Scr

[Time Frame: Baseline, 22days,3 months and 6 months]

12. Change in biological parameter: e-GFR

Variation between baseline to 6 months of Biological parameter among control and telemedicine groups: e-GFR

[Time Frame: Baseline, 22days,3 months and 6 months]

Other Pre-specified Outcome Measures:

13. Change in scores measured by Self-rating Depression Scale

Self-rating Depression Scale includes 20 items in four dimensions of psychological disorders, namely, psychotic emotional symptoms, somatic disorders, psychomotor disorders, and depression. The maximum value of SDS is 50 points. A lower total score means a better situation in terms of depression and vice versa

[Time Frame: Baseline, 22days,3 months and 6 months]

14. Number of hypoglycemia events

Hypoglycemia events for telemedicine group versus control group

[Time Frame: 6 months]

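### The between-arm count of hypoglycaemia events (outcome 14) is open to detection bias: no event definition, source or denominator is given, and glucose is collected on a denser schedule in the telemedicine arm

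*Protocol*

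**What the plan says.** Under Outcome Measures, outcome 14 is the number of hypoglycaemia events, described as "Hypoglycemia events for telemedicine group versus control group" with a 6-month time frame. It sits under the heading "Other Pre-specified Outcome Measures", below the primary and secondary outcomes. No glucose threshold, symptom criterion, source of events or denominator is given.

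The Detailed Description (Study Description) sets different glucose schedules for the two arms:

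- **Telemedicine:** patients upload values at four time points (fasting and after each of three meals). The schedule is "Data collection frequency: first three months, 4 times/week; 4-6 Month, 2 times/week".
- **Control:** "The control group will be followed up by telephone/outpatient clinic every 1 week", by telephone only during the lockdown. The same four time points are collected, but the number of days that one contact covers is not stated.

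The same section also gives a common schedule: "The clinical data of the two groups of patients will be collected at baseline, 22 days, 3 months, and 6 months respectively". Frequency of hypoglycaemia is in the list of data collected then. The trial is open label (Study Design).

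**The concern.** A low value that causes no symptoms is recorded only if someone measures at that moment. If the protocol has one arm measure and submit glucose more often, the same true rate of lows can yield more recorded events in that arm. Randomisation does not balance this, because the measurement schedule is part of the assigned intervention. Nor can a later analysis recover lows that were never measured in the control arm.

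Outcome 14 is the only listed outcome that counts an adverse event, and under Arms and Interventions doctors adjust medication through the telemedicine system. A spurious excess could mark the intervention as less safe than usual care, and a true reduction could be hidden.

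**Working it through.** The protocol gives no hypoglycaemia rate, significance level or sample size calculation, so there is no figure of its own to reproduce.

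**1. Scheduled collections.** Inputs from the Detailed Description: 4 per week for three months and then 2 per week (telemedicine); 1 per week (control); 6 months taken as 26 weeks.

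- Telemedicine: 13 × 4 + 13 × 2 = 78
- Control: 26 × 1 = 26
- Ratio: 78 / 26 = 3.0, or 4 × 78 = 312 versus 4 × 26 = 104 values at four per collection

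By period, the ratio is 4:1 in months 1–3 and 2:1 in months 4–6.

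**2. Days covered by a control contact.** If one weekly contact gathers k days of values, the ratio is 78 / (26 × k):

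- k = 1: 3.0
- k = 2: 1.5
- k = 3: 1.0

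The protocol does not state k. Above three days the ratio would fall below 1 (for k = 7, 78 / 182 = 0.43), so the direction of the imbalance also rests on k being small.

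**3. How much of the imbalance reaches the count.** Take k = 1. Let s be the share of control-recorded events that both arms would record equally, such as symptomatic events, and let the rest scale with collections. With no true difference, the apparent rate ratio is s + (1 − s) × 3:

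| s | Apparent ratio |
|---|---|
| 0 | 3.0 |
| 0.5 | 2.0 |
| 0.75 | 1.5 |
| 0.9 | 1.2 |
| 1 | 1.0 |

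**4. Illustrative false-positive rates.** All of the following is assumed except the total of 99 enrolled: equal true rates; negative binomial counts with dispersion 1; 50 and 49 patients per arm; an unequal-variance test of mean counts at two-sided 5%. Probability of declaring a difference, by simulation:

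| Apparent ratio | 0.1 control events per patient | 0.3 control events per patient |
|---|---|---|
| 1.2 | about 5% | about 7% |
| 1.5 | about 10% | about 17% |
| 2 | about 21% | about 44% |
| 3 | about 52% | about 87% |

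The result depends strongly on the assumed event rate and on the apparent ratio, and the protocol fixes neither.

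**The case against.** The strongest reply is that the link from uploads to events is not in the text. The protocol describes uploads as the basis for guidance on diet, exercise and medication, and nowhere says that hypoglycaemia is counted from them. It lists frequency of hypoglycaemia among data collected from both arms on the same visit schedule. The scheduled readings are fasting and after meals, so nocturnal or between-meal events need not scale with the number of uploads. An event definition may also stand in a statistical analysis plan that is not shown.

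Much of this stands. A reader might infer that the comparison is biased threefold, or that a false safety signal is likely. The documents do not support either. The factor of 3 needs every event to be found only through collected values and each control contact to cover a single day. The higher false-positive rates need that and an assumed event rate as well.

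The reply does not remove the concern. A patient asked about hypoglycaemia at a common visit can report only lows that were felt or measured, and the arm scheduled to measure more will know of more asymptomatic ones. Nothing in the outcome as written restricts the count to events that both arms would detect equally. An analysis plan could narrow the definition, but the unequal schedule is fixed in the protocol.

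**Conclusion.** The concern holds in a limited form. Outcome 14 is open to detection bias, probably towards more recorded events in the telemedicine arm. With no true difference, the apparent rate ratio lies between 1.0 and 3.0, provided that a weekly control contact covers one to three days of values. Where it falls depends on the event definition, the source of events and the days per contact, none of which the protocol states. The false-positive rates show only that a moderate ratio could matter; they are not estimates for this trial.

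Severity is moderate. The outcome is in the lowest tier, and the primary HbA1c comparison does not depend on it.

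**What to change.** State what counts as a hypoglycaemia event and where events are taken from. Base the between-arm comparison on symptomatic events or events needing assistance, asked in the same way in both arms at the existing 22-day, 3-month and 6-month visits. Report low values found only by measurement separately, as a rate per glucose reading submitted, and label them descriptive. State also how many days of values a weekly control contact collects.

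Study Status records the trial as completed, so this now concerns analysis and reporting. It can be done only as far as symptoms, need for assistance and reading counts were recorded, and the protocol does not say that they were. If they were not, report the count with its unequal ascertainment stated and without a claim about relative safety. The price is fewer countable events and less precision.

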## Eligibility

Minimum Age: 18 Years

Maximum Age: 55 Years

Sex: All

Gender Based:

Accepts Healthy Volunteers: No

Criteria: Inclusion Criteria:

- Physician diagnosis of Type 2 diabetes for more than 6 months
- 7.0%#HbA1c#10.0%
- Quarantine for 21 days due to COVID-19 outbreak related reasons
- age: 18 ~ 55 yrs
- BMI≥24
- Be able use smart phones and the Internet

Exclusion Criteria:

- Insulin pump users
- For female subjects: pregnancy or lactation, or subject may become pregnant during the study

- Patient who underwent obesity surgery to the exclusion of a gastric band, loosened or removed for more than a year
- Patients diagnosed with COVID-19 infection
- Have severe complications (chronic heart disease, cerebrovascular disease, diagnosed HIV/AIDS, cancer, emphysema, chronic liver or kidney disease) that would affect the subjects' ability to follow the tailored advice

## IPDSharing

Plan to Share IPD:

